##### LOWN Classification of Tachycardial Arrhythmia

|            |                           |
|------------|---------------------------|
| Class 0    | No VES                    |
| Class I    | Less than 30 VES per hour |
| Class II   | More than 30 VES per hour |
| Class IIIa | Polytope VES multifocal   |
| Class IIIb | Bigeminy                  |
| Class IVa  | 2 consecutive             |
| Class IVb  | ≥ 3 consecutive           |
| Class V    | R-T Phenomena             |

#### 6.3.2.5 *12-Lead Electrocardiogram*

Twelve-lead ECGs will be performed in accordance with the Schedule of Assessments (assessment screening, ICU, Hospital Discharge, 6 months post-OP, 24 months post-OP). ECG measurements should be recorded as AEs or SAEs if there are increases in QT/QTc >500ms or of >60ms over baseline.

- Date of performance
- Frequency beats per min.
- Sinus rhythm yes/no
- Cardiac arrhythmia yes/no

- Absolute arrhythmia (atrial fibrillation) yes/no, frequency per min.
- Atrial flutter yes/no
- SVES yes/no, number
- Prolonged QT Interval yes/no
- VES yes/no
- Bigeminy yes/no
- Couplets yes/no
- Triplets yes/no
- AV-Block yes/no, grade I, II, III
- Right bundle branch block yes/no
- Left bundle branch block yes/no
- Isoelectric ST yes/no; if no, elevation/decrease in: V1, V2, V3, V4, V5, V6, I, II, III, aVR, aVL, aVF
- Negative T-waves: yes/no; if yes: terminal/preterminal: V1, V2, V3, V4, V5, V6, I, II, III, aVR, aVL, aVF
- Lack of R-spike: no/yes; if yes: V1, V2, V3, V4, V5, V6, I, II, III, aVR, aVL, aVF
- Pathological Q-Spike: no/yes; if yes V1, V2, V3, V4, V5, V6, I, II, III, aVR, aVL, aVF

#### 6.3.2.6 General Medical History

General medical history of patients will be documented as follows (ascertainment not older than 24 hrs) :

- Head, no/yes, if yes: describe
- Thorax, no/yes, if yes: describe
- Abdomen, no/yes, if yes: describe
- Neurological/psychological history, no/yes, if yes: describe
- Musculoskeletal system, no/yes, if yes: describe
- Blood and hematopoietic system, no/yes, if yes: describe
- Wound infection, no/yes, if yes: describe
- Claustrophobia, yes, if yes: describe

#### 6.3.2.7 Cardiac Medical History

Cardiac medical history will be documented with grade (0 = no event, I = asymptomatic, II symptomatic, but no specific treatment, III = symptomatic and treatment necessary, IV = life-threatening):

- AV-Block I, II, III
- Sinus bradycardia
- Supraventricular arrhythmia
- Ventricular arrhythmia
- Vasovagal syncope
- Left ventricular failure
- Myocardial ischemia
- Cerebral ischemia
- Myocarditis

- Pericardial effusion, pericarditis

#### *6.3.2.8 Risk Factors*

Risk factors for coronary diseases of the patients will be documented:

- Date of last myocardial infarct
- Angina prior to myocardial infarct, if applicable: duration in months
- Prior myocardial infarcts, no/yes, if yes: how many months ago and localization (anterior, lateral, inferior)
- Prior PCI and/or stent, no/yes; if yes: vessels (LAD territory, LCX territory, RCA territory)
- Heart failure prior to myocardial infarct, no/yes
- Family disposition: arterial hypertension no/yes; Diabetes mellitus no/yes
- Smoking (never, previously, currently); number of pack-years
- EuroSCORE (logistic in %; [www.euroscore.org/calcge.html](http://www.euroscore.org/calcge.html)) will be determined

#### *6.3.2.9 Unwanted Tissue Changes*

During cardiac MRI and echocardiography-examinations there will be a special check for unwanted tissue changes.

## **7 STUDY CONDUCT**

### **7.1 Schedule of Observations**

The schedule of assessments is provided in Table 2.

**Table 2: Schedule of Assessments**

| Assessments                                    | I               | Ia                         | II             | IIa             | III                                | IV                                  | V                            | VI                                  |
|------------------------------------------------|-----------------|----------------------------|----------------|-----------------|------------------------------------|-------------------------------------|------------------------------|-------------------------------------|
|                                                | Screening       | BM transfer/
Cell Prep. | Intra-OP       | Post OP
/ICU | Hospital
Discharge e | 3-Month
FU e          | 6-Month FU/
Early termin. | 24-Month
FU                      |
| Timepoint                                      | Day -7
to -1 | Day -2 to 0                | Day 0          | Day 1           | Within 72 hrs
of discharge      | Month 3 e
(± 2 weeks) | Month 6
(±2 weeks)        | Month 24 d
(±2 weeks) |
| Informed consent                               | X               |                            |                |                 |                                    |                                     |                              |                                     |
| Patient Demographics                           | X               |                            |                |                 |                                    |                                     |                              |                                     |
| Inclusion/exclusion criteria                   | X               |                            |                |                 |                                    |                                     |                              |                                     |
| Medical history: general/cardiac /risk factors | X               |                            |                |                 |                                    |                                     |                              |                                     |
| Physical examination: general/vital signs      | X               |                            |                |                 | X                                  |                                     | X                            | X                                   |
| Cardiac examination:                           |                 |                            |                |                 |                                    |                                     |                              |                                     |
| NYHA and CCS criteria                          | X               |                            |                |                 | X                                  |                                     | X                            |                                     |
| Heart catheterization                          | X               |                            |                |                 |                                    |                                     |                              |                                     |
| Holter (VES, SVES), LOWN                       | X               |                            |                |                 | X                                  |                                     | X                            | X                                   |
| 12-lead ECG                                    | X               |                            |                | X               | X                                  |                                     | X                            | X                                   |
| Cardiac MRI scan                               | X               |                            |                |                 | X                                  |                                     | X                            |                                     |
| Echocardiography                               | X               |                            |                |                 | X                                  |                                     | X                            | X                                   |
| Laboratory:                                    |                 |                            |                |                 |                                    |                                     |                              |                                     |
| Serology                                       | X               |                            |                |                 |                                    |                                     |                              |                                     |
| Serum pregnancy test c              | X               |                            |                |                 |                                    |                                     |                              |                                     |
| HAMA g                              | X               |                            |                |                 |                                    |                                     |                              |                                     |
| Hematology, Chemistry, Electrolytes            | X               |                            |                | X b  | X                                  |                                     | X                            | X                                   |
| Blood Lipids                                   | X               |                            |                |                 |                                    |                                     |                              |                                     |
| NT-proBNP                                      | X               |                            |                |                 | X                                  |                                     | X                            | X                                   |
| QoL questionnaires a                | X               |                            |                |                 |                                    | X                                   | X                            | X                                   |
| 6MWT                                           | X               |                            |                |                 | X                                  |                                     | X                            |                                     |
| Bone marrow aspiration/blood sample            |                 | X                          |                |                 |                                    |                                     |                              |                                     |
| Randomization to treatment                     |                 | X                          |                |                 |                                    |                                     |                              |                                     |
| Cell/placebo preparation                       |                 | X                          |                |                 |                                    |                                     |                              |                                     |
| Cell/placebo transfer                          |                 | X                          |                |                 |                                    |                                     |                              |                                     |
| Injections of study treatment/ CABG            |                 |                            | X              |                 |                                    |                                     |                              |                                     |
| MACE                                           |                 |                            |                |                 |                                    |                                     | X                            | X                                   |
| Concomitant medications                        | X               | X                          | X f | X               | X                                  | X                                   | X                            | X                                   |
| Adverse events/Serious Adverse Events          | X               | X                          | X              | X               | X                                  | X                                   | X                            | X                                   |

a = SF 36 & MLHF-Q, EQ-5D; b = 36 hours after OP; after 0, 6, 12, 24 hours only CK, CK-MB, TNT. c = For female patients of childbearing potential only, d = 18 months after study finalization, e = patients receive dates for follow-ups, f = surgery standard medication will not be documented, g = only for patients with known hypersensitivity or sensitization against murine products;

Abbreviations: CCS= Canadian Cardiovascular Society, ECG=electrocardiogram, MACE= major adverse cardiovascular events, MRI= magnetic resonance imaging, NYHA=New York Heart Association, 6MWT=6-minute walk test, QoL=Quality of Life, SVES=supraventricular extrasystoles, VES=ventricular extrasystoles;

## 7.2 Observations by Visit

### 7.2.1 *Screening (Assessment I; Day -7 to Day -1)*

- Inform patient about clinical trial (record in appropriate documentation)
- Obtain written informed consent, record date and time of informed consent (see Section 9.7)
- Demographic details: height in cm, year of birth, gender
- General medical history (see Section 6.3.2.6)
- Cardiac medical history (see Section 6.3.2.7)
- Risk factors (see Section 6.3.2.8)
- In- and exclusion criteria (see Sections 4.1 & 4.2)
- Vital signs (see Section 6.3.2.2)
- General physical examination (see Section 6.3.2.3)
- Blood sampling for serology (see Section 6.3.2.1)
- Blood sampling for laboratory tests (see Section 6.3.2.1)
- Blood sampling for NT-proBNP (pg/mL; to be sent to Core Lab) and HAMA in case of known hypersensitivity (see Section 6.3.2.1)
- Serum pregnancy test (female patients of childbearing potential only, see Section 6.3.2.1)
- Cardiac MRI scan and echocardiography to be sent to Core Lab (see Sections 6.1.1 & 6.1.2, 6.1.5 & 6.1.6), value for LVEF within 12 hours from MRI Core Lab
- Classification of heart failure with NYHA and angina with CCS (see Section 6.1.3)
- Heart catheterization (see Section 6.1.4)
- Holter and LOWN classification (historic data may be used, see Section 6.3.2.4)
- 12-lead ECG (see Section 6.3.2.5)
- Completion of QoL questionnaires (MLHF and SF-36; see Section 6.2)
- 6-Minute Walk Test (6MWT, see Section 6.1.7)
- Documentation of AEs/SAEs during screening procedure (see Section 6.3.1)
- Concomitant medication, platelet aggregation inhibitors during the last 2 weeks (see Section 5.7)
- Determine patient's eligibility for enrollment (PI and study physician or at least two study physicians). Give reason in case patient is not eligible.

### 7.2.2 *Bone Marrow Transfer /Preparation of Cell Product/Placebo (Assessment Ia; Day -2 to 0)*

- Bone marrow aspiration and 20 mL blood sample collection for preparation of autologous serum (see Section 5.8). Transferring data in form "Transfer Protocol":
  - Serologic data (seronegative/seropositive)
  - Date and time of bone marrow harvest
  - Bone marrow volume (mL)
  - Date and time of blood sample taking
  - Blood sample volume
  - Date, time of start (handover to carrier) and end of transport from OP to stem cell laboratory

- Transfer of cells to the stem cell laboratory for processing
- Randomization to study treatment group performed by the cell processing laboratory
- Cell/placebo preparation according to validated SOPs
- Transfer of investigational drug from stem cell laboratory to OP with "Transfer Protocol"
- Documentation of data in "Transfer Protocol"
  - Date, time of start and end of transport from stem cell laboratory to OP at study site
  - Date and time of receiving investigational drug at OP, department, names of study nurse and physician
  - Confirmation of receipt of sealed randomization code envelope
  - Copy of "Transfer Protocol" into CRF
- Documentation of any change in concomitant medication
- Documentation of any AE/SAE since last assessment
- Data transfer into "Cell Preparation Form" to be performed after last patient out only:
  - Allocation of randomization No. to CD133+ cell preparation group or placebo group
  - Volume of bone marrow aspirate after filtration (200 µm) in mL
  - Volume of "final product" after resuspension in saline/autologous serum in mL
  - Recovery of CD 133+ cells in "final product" compared to bone marrow
  - Log depletion of non-target cells
  - Total viable CD 133+ cells in 5 mL syringes ("Final product ready for injection")
  - Bacterial contamination: results of quick test and sterility test

### 7.2.3 *Intra OP: Surgical Operation (Assessment II; Day 0)*

#### During the CABG Operation

- Date of surgery, time start and end of OP
- Number and distribution (RIVA, RCX, RCA) of distal anastomoses
- Number of myocardial injections of study treatment (15 injections planned; see Section 5.2 and Figure 5)
- Quantity of 5 mL completely injected, documentation of actual quantity (if applicable)
- Localization of injections according to Figure 5
- Bypass time (min.)
- Cross clamp time (min.)
- Documentation of low cardiac output (if yes: cardiac output < 2 (L/min/m^2) body surface? no/yes)
- Documentation of mechanic assist device if applicable
- Documentation of concomitant medication for treatment of an AE/SAE; standard medication (narcotics etc.) will not be documented,
- Documentation of any AE/SAE since last assessment

#### **7.2.4 *Post OP/Intensive Care Unit (Assessment II a; Day 0 to Day 4 approx.)***

##### Post-operation/ICU

Blood sampling for laboratory tests at 0, 6, 12, 24 hours post-operation (only three values)

- Clinical Chemistry:
  - Creatine Kinase (CK) (U/l)
  - Creatine Kinase MB (CK-MB) (U/l)
  - Troponin T (TNT) (µg/l)
- Blood sampling for laboratory tests at 36 hours post-operation
  - Hematology (see Table 1)
  - Clinical Chemistry (all, see Table 1)
  - Electrolytes (see Table 1)
- Performance of 12-lead ECG (see Section 6.3.2.5)
- Documentation of any perioperative infarction
  - If applicable: Localization of myocardial infarct (LV/RV; if LV: septal, anterior, posterior, lateral, anterolateral)

##### End of Intensive Care Unit

- Length of stay (days)
- Ventilation (hours)
- Catecholamines and Inotropics (adrenaline, noradrenaline, dopamine, dobutamine, PDE-inhibitor, Ca-sensitizer; maximum in µg/kg/min)
- Documentation of concomitant medication for treatment of an AE/SAE
- Documentation of any AE/SAE since last assessment

#### **7.2.5 *Hospital Discharge: (Assessment III; within 72 hrs of discharge)***

- Vital signs (see Section 6.3.2.2)
- General physical examination (see Section 6.3.2.3)
- Blood sampling for laboratory tests (Hematology, Clinical Chemistry and Electrolytes; see Section 6.3.2.1)
- Blood sampling for NT-proBNP (pg/mL; to be sent to Core Lab; see Section 6.3.2.1)
- Cardiac MRI scan and echocardiography to be sent to Core Lab (see Sections 6.1.1 & 6.1.2, 6.1.5 & 6.1.6)
- Classification of heart failure with NYHA and angina with CCS (see Section 6.1.3)
- Holter and LOWN classification (see Section 6.3.2.4)
- 12-lead ECG (see Section 6.3.2.5)
- 6-Minute Walk Test if reasonable (6MWT, see Section 6.1.7)
- Date of discharge, where to (home, other hospital, rehabilitation)
- Documentation of any change in concomitant medication
- Documentation of any AE/SAE since last assessment
- Provide patient with dates for telephone call after 3 months post-OP (study pass)
- Provide patient with dates for cardiac MRI, echocardiography, and Holter appointments after 6 months post-OP (study pass)

### 7.2.6 *Follow-Up Period*

Prior to Assessment IV QoL questionnaires and addressed envelope should be sent to patients so that they can complete the questionnaires at home.

#### 7.2.6.1 *3-Month Follow-Up post OP ( $\pm 2$ weeks, Assessment IV, per telephone)*

- Date of telephone call
- Patient able to perform assessment? If not, give reasons: hospitalization or unknown (in case patient has deceased, do not fill out 3-Month Follow-Up but proceed to 6-Month Follow-Up/Early Termination)
- Retrieve QoL questionnaires; if not returned to hospital at time of Assessment IV remind patient to complete form (see Section 6.2)
- Confirmation of dates for next follow-up
- Documentation of any change in concomitant medication
- Documentation of any AE/SAE since last assessment

#### 7.2.6.2 *6-Month Follow-Up post OP ( $\pm 2$ weeks, Assessment V)/Early Termination*

- Study termination
  - has the study been terminated according to protocol? If yes, proceed with Physical examination/vital signs
  - If study was early terminated:
    - Date of withdrawal/early termination
    - Reason for withdrawal/early termination (AE, at the discretion of the investigator, violation of eligibility criteria, deviation from the treatment plan specified in the protocol, pregnancy, patient withdraws consent, death, other (describe))
- Date of patient contact
- Vital signs (see Section 6.3.2.2)
- General physical examination (see Section 6.3.2.3)
- Blood sampling for laboratory tests (Hematology, Clinical Chemistry and Electrolytes; see Section 6.3.2.1)
- Blood sampling for NT-proBNP (pg/mL; to be sent to Core Lab; see Section 6.3.2.1)
- Cardiac MRI scan and echocardiography to be sent to Core Lab (see Sections 6.1.1 & 6.1.2, 6.1.5 & 6.1.6)
- Classification of heart failure with NYHA and angina with CCS (see Section 6.1.3)
- Holter and LOWN classification (historic data may be used, see Section 6.3.2.4)
- 12-lead ECG (see Section 6.3.2.5)
- Determination of MACE (see Section 6.3.1.6)
- Completion of QoL questionnaires (MLHF and SF-36; see Section 6.2.)
- 6-Minute Walk Test (6MWT, see Section 6.1.7)
- Documentation of any change in concomitant medication
- Documentation of any AE/SAE since last assessment

*7.2.6.3 24-Month Follow-Up post OP ( $\pm$  2 weeks, Assessment VI after data closure for safety reason)*

- Date of patient contact
- Vital signs (see Section 6.3.2.2)
- General physical examination (see Section 6.3.2.3)
- Echocardiography from practice based cardiologist (see Sections 6.1.1, 6.1.2, & 6.1.6)
- Holter from practicing cardiologist and LOWN classification (see Section 6.3.2.4)
- Blood sampling for laboratory tests (Hematology, Clinical Chemistry and Electrolytes; see Section 6.3.2.1)
- Blood sampling for NT-proBNP (pg/mL; to be sent to Core Lab; see Section 6.3.2.1)
- Completion of QoL questionnaires (MLHF and SF-36; see Section 6.2.)
- Performance of 12-lead ECG (see Section 6.3.2.5)
- Determination of MACE (see Section 6.3.1.6)
- Documentation of concomitant medication related to treatment of AE/SAE
- Documentation of any AE/SAE and reporting of any SAE that is related to the investigational product (relatedness 3 to 5) since last assessment; documentation of any MACE and any Event of Specific Interest since last assessment (reporting only in case of relatedness 3 to 5); see Section 6.3.1, 6.3.1.5, and 6.3.1.6

## 8 STATISTICAL METHODS

Before unblinding, a separate statistical analysis plan (SAP) will be finalized, providing detailed methods for the analyses outlined below. Analyses will be performed after database lock.

Any deviations from the planned analyses will be described and justified in the final integrated study report.

### 8.1 Study Patients

#### 8.1.1 *Disposition of Patients*

The number and percentage of patients entering and completing each phase of the study will be presented, stratified by treatment. Reasons for withdrawal pre- and post-randomization will also be summarized.

#### 8.1.2 *Protocol Deviations*

Every deviation from the trial protocol must be specified and documented in writing separately for each patient. The Investigator has to report the protocol deviation to the sponsor. The Investigator must consult with the monitor and discuss the type and extent of deviation as well as the possible consequences for further participation of the patient in the study. If the evaluability of a patient is questionable the national coordinating Investigator, the trial site principal Investigator and the biometrician will be consulted. Major violations leading to exclusion from the PPS (Per Protocol Set) will be defined during the blind review meeting and in agreement with the Sponsor after data cleaning but before database closure and before breaking the randomization code.

One of the following surgical complications will lead to post-hoc exclusion from the study:

- Perioperative cerebral ischemic insult with persisting relevant neurologic deficit
- Deep sternal wound infection
- Rare surgical complications (i.e. respiratory failure with need for prolonged mechanical ventilation, intestinal infarction, several acute pancreatitis, chronic chylothorax, aortic dissection, peripheral ischemia requiring surgery)

Patients with one or more major protocol violations will be excluded from PPS group leading to the exclusion of all efficacy data from the PPS analysis, if one of the following criteria is fulfilled:

- Patients without measurement after 6 months for LVEF
- Violation of inclusion or exclusion criteria.

Number of patients with protocol deviations during the study and listings describing the deviations will be provided. Patients that are not attendant at study visits or refuse to undergo certain assessments are non-compliant with the study protocol. Listings and frequency tables of those patients will be provided.

The insufficiency of CD133+ cell counts (less than  $0.5 \times 10^6$  but  $\geq 0.1 \times 10^6$ ) will lead to post-hoc exclusion from the study but patients will be followed-up similar to the intend-to-treat population.

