### 8.1.3 *Analysis Populations*

Two different sets of patients will be defined to perform analyses. A “Full Analysis Set” (FAS) following the principle of intent-to-treat (ITT) will include every patient as randomized and compare the patients according to the group to which they were randomly allocated, regardless of patients' compliance, or withdrawal from the study. It is the most cautious approach and so minimizes type 1 error, helps preserve prognostic balance in the study arms and allows for the greatest generalizability.

Secondly, an analysis of all per protocol treated patients will be performed. The “Per Protocol Set” (PPS) is a subset of the FAS patients who are compliant with the study protocol. The PPS sample will consist of all subjects from the FAS group without any major protocol violation.

First and foremost, confirmatory analyses on primary efficacy variable will be performed on the FAS patients but a secondary analysis will also be performed based upon the Per Protocol Set, to assess the sensitivity of the analysis to the choice of analysis population. The ITT analysis will be considered as the primary one.

Patients who received the cellular product or Placebo but dropped-out post-hoc because of cell count insufficiency will be evaluated separately.

The safety population will comprise all patients randomized into the study, in which each patient's treatment is as taken on the study. Safety evaluations will be performed on the safety population.

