| Ventricular arrhythmia                                                                          |  |  |            |          |  |  |
| Vasovagal syncope                                                                               |  |  |            |          |  |  |
| Left ventricular failure                                                                        |  |  |            |          |  |  |
| Myocardial ischemia                                                                             |  |  |            |          |  |  |
| Cerebral ischemia                                                                               |  |  |            |          |  |  |
| Myocarditis                                                                                     |  |  |            |          |  |  |
| Pericardial Effusion, Pericarditis                                                              |  |  |            |          |  |  |
| Deep sternal wound infection                                                                    |  |  |            |          |  |  |

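### Section 8.1.2 excludes patients with listed peri-operative complications from the study, which conflicts with the all-randomised primary set in section 8.1.3 and leaves their follow-up unstated

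*Protocol*

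**What the plan says.** Section 8.1.2 of the protocol contains three separate exclusion rules.

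- **Surgical complications.** "One of the following surgical complications will lead to post-hoc exclusion from the study". The list opens with "Perioperative cerebral ischemic insult with persisting relevant neurologic deficit", continues with deep sternal wound infection, and ends with rare events such as respiratory failure needing long ventilation, bowel infarction, aortic dissection and limb ischemia requiring an operation.
- **Per-protocol set (PPS).** "Patients with one or more major protocol violations will be excluded from PPS group", with two criteria: no 6-month LVEF, or breach of an eligibility criterion. The surgical complications are not among them.
- **Low cell count.** This "will lead to post-hoc exclusion from the study but patients will be followed-up similar to the intend-to-treat population".

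Section 8.1.3 defines the full analysis set (FAS), which "will include every patient as randomized and compare the patients according to the group to which they were randomly allocated", whatever their compliance or withdrawal. It adds: "The ITT analysis will be considered as the primary one". The safety population is all randomised patients.

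Appendix 2 lists "Cerebral ischemia" and "Deep sternal wound infection" among the adverse events of specific interest. Section 6.3.1.5 requires these to be documented up to Assessment VI at 24 months.

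**The concern.** Randomisation takes place at Assessment Ia, before surgery (section 4.5). The listed complications therefore follow randomisation, and most follow the intramyocardial injection as well. They may be affected by treatment, so removing patients because of them selects on an outcome. An all-randomised primary analysis exists to prevent that.

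Two things are at stake. The first is who is in the confirmatory comparison of LVEF at 6 months: section 8.1.2 removes patients whom section 8.1.3 requires. The second is what is learned about these patients later. The low-cell-count rule keeps follow-up in so many words, while the complication rule is silent. If exclusion is handled as withdrawal, the duty to report SAEs ends 30 days after injection (section 6.3.1.3.2).

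**Working it through.** **Design figure.** Section 8.7 assumes a difference of 4.5 LVEF points, SD 7.5, two-sided α of 0.05 and 90% power. With the non-central t distribution (df = 2n − 2, non-centrality (4.5/7.5)·√(n/2)), power is 0.898 at n = 59 and 0.903 at n = 60. So 60 per group is right. With 15% drop-out, 60/0.85 = 70.6, rounded up to 71 per group, or 142 in total. The stated figures reproduce.

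**Does exclusion from the study mean only the PPS?** Three points in the text speak against it.

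1. The PPS criteria form their own list in section 8.1.2, and the complications are not on it.
2. The same phrase is used for low cell counts. Those patients are treated as drop-outs (section 3.3), evaluated separately (section 8.1.3) and may be replaced (section 4.3). There the phrase means more than leaving the PPS.
3. The blind-review step in section 8.1.2 is written for major violations leading to PPS exclusion. It is not tied to the complication list.

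**Does nominal FAS membership rescue the comparison?** Only if the 6-month MRI is still done. Section 8.2 replaces no missing values. A patient removed before that scan has no primary outcome and adds nothing to the ANCOVA, even if counted in the FAS. Section 4.3 calls for Early Termination evaluations after premature withdrawal, and these include an MRI (section 7.2.6.2). The protocol does not say that an earlier scan stands in for the 6-month value.

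**Follow-up periods side by side.**

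- SAE reporting after withdrawal: to 30 days after injection (section 6.3.1.3.2).
- Events of specific interest: to 24 months (section 6.3.1.5).
- MACE: assessed at 6 and 24 months (section 6.3.1.6).
- After a listed complication: nothing stated.

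**Size.** The protocol gives no rate for these complications and no LVEF for patients who have them. What follows is illustration on assumed inputs. Let q_c and q_p be the excluded shares in the cell and placebo arms, and D the LVEF deficit of excluded against retained patients, taken as equal in both arms. Excluding them shifts the estimated difference by (q_c − q_p) × D, in favour of the arm with more exclusions.

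| q_c vs q_p (assumed) | D (assumed) | Shift in LVEF points | Share of 4.5 |
|---|---|---|---|
| equal | any | 0 | 0% |
| 5% vs 2% | 5 | 0.03 × 5 = 0.15 | 3% |
| 8% vs 3% | 10 | 0.05 × 10 = 0.50 | 11% |
| 10% vs 3% | 10 | 0.07 × 10 = 0.70 | 16% |

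Swapping the arms reverses the sign.

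**Power**, if such losses came on top of the 15% allowance (again assumed): 2% extra leaves 58 per group and power 0.893; 5% leaves 57 and 0.888; 10% leaves 54 and 0.871. The loss is small.

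**The case against.** The strongest reply is that section 8.1.3 already settles the matter. The FAS holds every randomised patient regardless of withdrawal, so leaving the study does not remove anyone from the primary set. The complication rule also stands under Protocol Deviations, between two PPS paragraphs, and may have been meant for the PPS. That intent is possible, but the wording does not express it, and an analyst following section 8.1.2 as written would drop these patients.

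A reader might infer that the rule deletes harms from the safety data. The documents do not support that. The safety population is all randomised patients. Section 8.6 plans a table of adverse events leading to withdrawal and a listing of all AEs. SAEs are reported to 30 days after injection even after withdrawal, and AEs are followed until resolved or stable (section 6.3.1.4). The complication that triggers exclusion would therefore be tabulated; only later information is at risk.

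A reader might also infer that an event cannot be both of specific interest and a reason for exclusion. It can be recorded and also end participation. Appendix 2 matters only because those events carry documentation to 24 months, which early exclusion could cut short.

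On bias, both arms receive the same 15 injections (section 5.2), so harm from the injection procedure itself would be expected in both. Treatment-team assessors are blinded, and section 5.4 has patients assigned to populations before the code is broken. This guards against deliberate selection by arm, but not against selection that follows from a true treatment effect. The assumed deficits are also generous: most listed complications are extracardiac, and 10 points exceeds the planning SD of 7.5.

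**Conclusion.** The point holds as a conflict between sections 8.1.2 and 8.1.3, together with a gap in stated follow-up. A written rule takes patients out of the study on events after randomisation, while the primary analysis requires them. With no replacement of missing values, its literal use removes them from the LVEF comparison.

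The stronger conclusion, that the trial would look better than it is by some calculable amount, does not follow. Bias needs a difference between arms in how often these events occur or in the LVEF of those affected, and the protocol gives neither. The 0.15 to 0.70 points above rest wholly on assumed inputs and could be zero or have the opposite sign. The case for correction rests on the contradictory definition of who is analysed, and does not depend on those figures.

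**What to change.** In section 8.1.2, replace exclusion from the study for the listed surgical complications with exclusion from the PPS only, decided at the blind review before the code is broken. Add a sentence that these patients stay in the FAS, the safety population and the MACE analysis, and that the planned 6-month MRI and 24-month safety follow-up continue for them. Sections 8.1.2, 8.1.3 and 6.3.1.3.2 should then be read together so that the 30-day limit after withdrawal is not applied to them.

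The cost is one paragraph. LVEF may vary slightly more when these patients are kept. The planned 60 evaluable per group and 142 randomised are unchanged.
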